### 2.12. Allocation Concealment Mechanism

To ensure proper allocation concealment, a statistician will be assigned to produce the allocation sequence list by using block randomization software. Each cluster will be given a unique code in a sealed opaque envelope. Following that, the research assistant will open the envelopes and assign the clusters to the intervention or control group based on the list of codes generated by the software. Moreover, to avoid bias at the individual level, the envelopes will be opened only after the school coordinator selects the required participant number, and after obtaining consent for treatment and collecting baseline data.

### 2.13. Statistical Analyses

IBM SPSS Software 25.0 (SPSS Inc. Chicago, IL, USA) will be used to analyze collected data. However, missing data will be managed by adopting the intention-to-treat analysis concept. Prior to analysis, continuous variables will be checked for normality. The alpha level of significance will be set at the value of <0.05. Descriptive analysis will be employed to describe the data at baseline. Regarding the between-group comparisons, the chi-square test will be applied to compare the frequency difference of categorical data of the intervention with that of the control groups. The independent-samples *t*-test will be applied to compare the mean difference of continuous data of the intervention with that of the control group. 

Furthermore, to evaluate the changes within both groups, Cochran’s Q test will be applied to test the frequency differences of categorical data within the study groups’ overtimes. The one-way repeated measures ANOVA will be applied to identify the mean difference within the study groups for continuous variables overtimes. Generalized estimating equations will be used to test the main effect and interaction between and within the overtimes of the intervention and control groups.

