### 2.7. Sample Size

For the sake of calculating the appropriate sample size for clustering, the standard sample size estimate for the individually randomized design will be calculated. This calculation process is done first by applying the formula to find the difference between two population proportions (power = 0.80, alpha = 0.05 two-sided), (P1 = 0.71, P2 = 0.43 [35]). Then it is inflated by the design effect (design effect = 1.4). The power calculations propose a minimum sample size of 47 participants per arm. This is done by taking into account 20% attrition and 10% expected proportion eligibility. Therefore, a minimum of 183 participants is required for this study.
(1)$$N\;=\;{\left\{1.96\surd 1.14*0.43\;+\;0.84\surd 0.21\;+\;0.25\right\}}^{2}/{\left(0.71\;-\;0.43\right)}^{2}\;=\;47$$

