### 2.8. Sampling Method

A total number of 12 schools with 183 participants that have met the inclusion and exclusion criteria will take part in the study. Following cluster sampling, six of the schools will be involved in the intervention group, while the other six are the control group. Then the proportionate allocation number of teachers to participate in the study will be calculated based on the density of the teachers in each school (probability proportional to size (PPS). Participants’ selection will be conducted by using a simple random sampling technique.

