### 2.11. Randomization

The unit of randomization in this current study is a school. To allocate the twelve eligible clusters (schools) to the study groups, an independent statistician will create the randomization sequence using the Sealed Envelope tool [38], with a 1:1 allocation using random block sizes of 2 and 4. Thus, six clusters were randomly allocated to the intervention group (VX9, XP6, EP9, ZI8, FF5, and IQ3) and six clusters to the control group (IO2, OM1, BM3, AT1, AA4, and KM3).

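### The chi-square and t-tests named in section 2.13 for between-group comparisons ignore school clustering; if the protocol's own design effect of 1.4 is right, their type I error is about 9% to 10%, not 5%

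*Protocol article*

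**What the plan says.** - **Design.** Section 2.11: "The unit of randomization in this current study is a school". Section 2.8 gives "A total number of 12 schools with 183 participants" and states that "six of the schools will be involved in the intervention group, while the other six are the control group".
- **Sample size.** Section 2.7 starts from an individually randomised comparison with "P1 = 0.71, P2 = 0.43", 80% power and two-sided alpha 0.05. It continues: "Then it is inflated by the design effect (design effect = 1.4". No ICC is given.
- **Between-group tests.** Section 2.13, under the subject of between-group comparisons and at alpha 0.05: "the chi-square test will be applied to compare the frequency difference of categorical data of the intervention with that of the control groups". For continuous data, the same part is played by the independent-samples t-test. Neither sentence mentions an adjustment for school.
- **GEE.** Section 2.13 ends: "Generalized estimating equations will be used to test the main effect and interaction between and within the overtimes of the intervention and control groups". The abstract names GEE as the method for differential change over time. Neither place says whether the cluster is the teacher or the school.

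**The concern.** By inflating the sample size, the plan accepts that teachers in one school resemble each other. The tests it then names for comparing the arms assume the opposite. The sample is enlarged to pay for clustering, and the tests discard the adjustment that it was meant to support.

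The consequence is standard errors that are too small, intervals that are too narrow, and too many false-positive claims. The primary outcomes in section 2.5.1 are mostly proportions, which is the type of data assigned to the chi-square test. The discussion says that the programme will be taken to other settings if it is shown to work, so a false-positive result would have consequences.

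**Working it through.** **Inputs from the article.** 12 schools, 6 per arm; 183 teachers, so 183/12 = 15.25 per school; design effect (DE) 1.4; two-sided alpha 0.05; proportions 0.71 and 0.43; 20% attrition; 10% eligibility allowance.

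**Assumptions.** Schools are of equal size. The article does not say which school size the 1.4 belongs to; 15.25 is used here.

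**Step 1. Reproduce the plan's figure.** The printed formula gives {1.96√(1.14 × 0.43) + 0.84√(0.21 + 0.25)}² / 0.28² = 48.1, against 47 stated. From 47 per arm: 47 × 1.4 × 2 / 0.8 / 0.9 = 182.8, rounded up to 183. So the 1.4 is built into the total of 183.

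**Step 2. Type I error of a test that ignores schools.** The true variance is DE times the variance that the test uses, so the error is 2 × (1 − Φ(1.96/√DE)).

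- DE 1.4: 1.96/1.183 = 1.656, error **9.8%**.
- Implied ICC: (1.4 − 1)/(15.25 − 1) = 0.028. After 20% attrition there are 15.25 × 0.8 = 12.2 per school, DE = 1 + 11.2 × 0.028 = 1.31, error **8.7%**.

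**Step 3. Range over assumed ICCs**, with DE = 1 + 14.25 × ICC:

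| ICC (assumed) | DE | Type I error |
|---|---|---|
| 0.01 | 1.14 | 6.7% |
| 0.02 | 1.29 | 8.4% |
| 0.05 | 1.71 | 13.4% |

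**Step 4. Simulation.** Beta-binomial data, 6 against 6 schools, true proportion 0.43 in both arms, one time point, 100,000 runs per row:

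| Teachers per school, ICC | Chi-square | School-clustered sandwich SE, uncorrected, z test | t-test on 12 school proportions (10 df) |
|---|---|---|---|
| 15, 0.028 | 9.6% | 9.9% | 5.1% |
| 12, 0.028 | 9.1% | 10.0% | 5.2% |

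The chi-square column agrees with step 2. The sandwich column shows that clustering on school is not enough by itself with 12 schools; the variance also needs a small-sample correction. The school-level t-test holds its level.

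**The case against.** **The GEE may already handle schools.** A reader might infer from the group-and-time description that the GEE has no school level, so that every between-arm analysis runs at about 10%. The article does not support this. A GEE clustered on school would also test group, time and their interaction, and a condensed article may leave the cluster variable to the full protocol or analysis plan. This part of the objection stands: the silence is not itself an error.

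**The 10% does not carry over to the group-by-time contrast.** Stable school effects largely cancel in a change score. As an illustration for a teacher-level analysis of a continuous outcome, assume 15.25 per school, ICC 0.028, and correlations over time of 0.8 for school effects and 0.5 for teachers. The ICC of change is (0.028 × 0.2)/(0.028 × 0.2 + 0.972 × 0.5) = 0.011, the design effect is 1 + 14.25 × 0.0114 = 1.16, and the error is 6.9%. It would be 5% with fully stable school effects and 9.8% if the two correlations were equal. The article gives neither correlation. This also stands.

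**The figure is conditional.** No ICC is stated, so the article gives no unconditional error rate, even for the chi-square test. This stands, and the range in step 3 is the answer to it.

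**The tests may be for baseline only.** Their sentences follow one on describing baseline data, and nowhere are they called the primary test. This reading is possible but less natural. They are introduced as the between-group comparisons, and the next paragraph pairs them with tests of change over time within groups. If baseline was all that was meant, the text should say so. As written, nothing says whether they or the GEE govern the conclusion.

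**Conclusion.** The point holds for the chi-square and independent-samples t-tests. They are stated in the article, not left to another document, and they contradict both the unit of randomisation and the sample-size premise. Their type I error is about 9% to 10% if the design effect of 1.4 is right, and 6.7% to 13.4% for assumed ICCs of 0.01 to 0.05. This rests on reading them as outcome tests.

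No error rate can be given for the GEE. Two conditional statements can be made. Clustering on the teacher would ignore variation between schools. Clustering on school with an uncorrected sandwich SE and a z test would run at about 10% at a single time point with 12 schools. Neither is shown to be the sponsor's choice.

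The wording should be corrected before the between-arm results are interpreted.

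**What to change.** In section 2.13:

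1. Limit the chi-square and independent-samples t-tests to describing the groups at baseline.
2. Base between-arm outcome inference on one named method that accounts for school and is valid for 12 clusters. Suitable examples are GEE clustered on school with a small-sample-corrected variance and a t reference with 10 degrees of freedom, or a t-test on the 12 school summaries (10 degrees of freedom).
3. State the GEE cluster unit if GEE is kept. Reporting the observed ICC would help readers judge the 1.4.

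**Cost.** Analysis wording only; no new data. Confidence intervals become wider. Under a design effect of 1.4 they widen by √1.4 = 1.18, which the sample size already allows for. Using t with 10 degrees of freedom adds a factor of 2.228/1.96 = 1.14, which section 2.7 does not allow for.

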## Abstract

Breast cancer is the most common cancer spread among women worldwide. Whereas many studies have discussed the significance of breast cancer screening among women in various countries, few have attempted to discuss this topic among female school teachers. As teachers educate and communicate with students, this may play an essential role in health education and in promoting healthy behavior, such as breast cancer screening. The primary goal of this study is to develop and implement an educational intervention of breast cancer screening and evaluate its effectiveness among Yemeni female school teachers in Malaysia. This was carried out as per the health belief model. A cluster-randomized controlled trial was conducted among 183 Yemeni female school teachers in twelve schools in Klang Valley, Malaysia. A random assignment of the target schools was made to include them within the intervention or control group. Participants in the intervention group were offered a 90-min session for one-day educational intervention on breast cancer screening. On the other hand, participants in the control group were offered the same educational materials at the end of the study. Relevant data was collected at baseline, one month following the intervention, and then three- and six-months follow-up assessments. Analysis of such data was done via IBM SPSS software 25.0 by generalized estimating equations (GEE) to assess the differential changes over time. A primary outcome embodied in breast cancer screening practice uptake was expected. Secondary outcomes include the target group’s knowledge on and beliefs of breast cancer screening. This study intends to contribute to the credibility and effectiveness of utilizing a theory-based breast cancer screening intervention in order to raise the awareness of women on conducting breast cancer screening.

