In brief, interventions focusing on BC early detection are less common among school teachers, in general, and absent among Yemeni school teachers in Malaysia, in particular. Therefore, not only does the current study intend to develop and evaluate an educational intervention based on the HBM but also to educate Yemeni female school teachers in Arabic schools in Malaysia and provide them with knowledge and enhance their beliefs of BC and BCS practice. It also aims to promote BCS among them.

The overall objective of this study is to develop and evaluate the effectiveness of an educational intervention grounded in the HBM on BCS uptake (BSE, CBE, and mammography), knowledge, and beliefs among Yemeni female school teachers in Klang Valley, Malaysia. It is hypothesized that starting from baseline until the three- and six-month assessment, women in the experimental group will gain the following: i.An increase in the proportion of their BCS uptakeii.An increase in their BC knowledge scoresiii.An improvement in their BC health beliefs (perceived susceptibility, perceived seriousness, perceived benefits, perceived barriers, health motivation, confidence).

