Furthermore, participants in the control group will not receive any education during the study period. However, they will be given the same educational materials on BCS at the end of the study, and they also will answer the same sets of the questionnaires at baseline, one month following the intervention, then after three- and six-months have gone by after the intervention. 

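### The within-arm tests and a GEE main effect that includes baseline should not carry the effectiveness claim; state the hypothesis against control and judge it on a baseline-adjusted between-arm contrast

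*Protocol article*

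**What the plan says.** Section 2.13 (Statistical Analyses) lists three families of tests and sets a single significance level of 0.05.

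- **Between arms, unadjusted.** "Regarding the between-group comparisons, the chi-square test will be applied to compare the frequency difference of categorical data". For continuous outcomes an independent-samples t-test "will be applied to compare the mean difference of continuous data of the intervention with that of the control group".
- **Within each arm.** Cochran's Q for categorical outcomes, and for continuous ones: "The one-way repeated measures ANOVA will be applied to identify the mean difference within the study groups for continuous variables overtimes". The stated purpose is "to evaluate the changes within both groups".
- **GEE.** "Generalized estimating equations will be used to test the main effect and interaction between and within the overtimes of the intervention and control groups". The Abstract says that the data are analysed "by generalized estimating equations (GEE) to assess the differential changes over time".

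The hypothesis in the Introduction is that "starting from baseline until the three- and six-month assessment, women in the experimental group will gain the following": higher screening uptake, higher knowledge scores and better health beliefs. It names no comparison with control.

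Section 2.3 says of the control participants that "they also will answer the same sets of the questionnaires at baseline" and again at one, three and six months. Section 2.12 has baseline data collected before the allocation envelopes are opened.

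**The concern.** A test of change within one arm does not use the randomisation. Change over time in the intervention arm combines the effect of the session with everything that both arms share: answering the same questionnaire four times, repeating the breast-model demonstration, and any general trend. The hypothesis is itself worded as change within the experimental arm. A significant repeated-measures ANOVA or Cochran's Q in that arm would therefore appear to confirm it even if control changed just as much.

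The GEE main effect has a different weakness. It does compare the randomised arms, but if it is averaged over all four occasions it includes one at which no effect is possible, because baseline precedes allocation. It then understates the effect.

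The risk is a claim of effectiveness that rests on shared change, or a diluted estimate reported as the treatment effect.

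**Working it through.** **Inputs from the article.** Four occasions: baseline, one, three and six months (Abstract, section 2.3). Planning proportions 0.71 and 0.43, so a difference of 28 percentage points (section 2.7). Total 183, with 20% attrition (section 2.7). Baseline before allocation (section 2.12).

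**The plan's own figure.** The two-proportion formula at 0.71 and 0.43, two-sided 0.05 and 80% power, gives 47.8 per arm against the stated 47. Then 2 × 47 × 1.4 / 0.8 / 0.9 = 182.8, so 183. The sample size reproduces to within one participant per arm, and the point does not depend on it.

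**1. Within-arm tests when the arms do not differ.** Suppose both arms change equally and each within-arm test has power q. The chance of significance in intervention but not in control is q(1 − q):

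| q | q(1 − q) |
|---|---|
| 0.2 | 0.16 |
| 0.5 | 0.25 |
| 0.8 | 0.16 |

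The maximum is 25%, at q = 0.5. The chance that exactly one arm, either one, is significant is 2q(1 − q) = 50% at q = 0.5, but half of those trials favour control.

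A simulation agrees. It used 73 per arm (183 × 0.8 / 2 = 73.2), normal data, four occasions, an assumed correlation of 0.5 between occasions, no clustering, no arm effect, and the same shift after baseline in both arms:

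| Shared shift (SD) | Intervention arm significant | Intervention significant, control not |
|---|---|---|
| 0 | 5% | 4% |
| 0.1 | 12% | 11% |
| 0.2 | 39% | 25% |
| 0.25 | 58% | 25% |
| 0.3 | 75% | 19% |
| 0.4 | 94% | 5% |

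The middle column bears on the hypothesis as worded. With a shared shift of 0.4 SD, the experimental arm shows a significant change in 94% of trials although the intervention does nothing.

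**2. Main effect averaged over baseline.** With no difference at baseline and a constant difference of 28 points at the three later occasions, the simple average is (0 + 28 + 28 + 28) / 4 = 21 points, or 75% of the effect.

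**3. Precision of a baseline-adjusted contrast.** The article gives no correlation r between baseline and follow-up, so 0.3, 0.5 and 0.7 are assumed. For a continuous outcome with equal variances, at the individual level and ignoring clustering, the variances are proportional to:

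- arm difference in change from baseline: 2(1 − r)
- arm difference at follow-up, adjusted for baseline: 1 − r²
- ratio, adjusted to change: (1 − r²) / (2(1 − r)) = (1 + r) / 2

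The ratio is 0.65, 0.75 and 0.85 at r = 0.3, 0.5 and 0.7, and it is below 1 for every r below 1.

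Against the main effect pooled over four occasions, signal divided by standard error, per SD of a constant effect and up to a common factor for sample size, is:

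| r | Main effect, 4 occasions | Adjusted, one follow-up | Adjusted, mean of 3 follow-ups |
|---|---|---|---|
| 0.3 | 0.77 | 0.74 | 1.06 |
| 0.5 | 0.67 | 0.82 | 1.10 |
| 0.7 | 0.60 | 0.99 | 1.27 |

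A single adjusted follow-up loses slightly to the pooled main effect at r = 0.3, because the latter uses three follow-ups. Over the same follow-ups the adjusted contrast wins throughout.

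**The case against.** The best defence is that section 2.13 already contains valid comparisons. The within-arm tests have a limited purpose, to evaluate change in each group. The same section lists between-arm tests, and the GEE sentence names the interaction, which the Abstract identifies as the purpose of the GEE. An arm-by-time contrast is a proper randomised comparison and suits a hypothesis about gain from baseline. The choice of covariates and the exact model can be left to an analysis plan that is not shown. All of this stands.

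A reader might therefore go too far in four ways:

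- *That effectiveness will be read only from the within-arm tests and the main effect.* No text says so, and the interaction and the between-arm tests are planned.
- *That the main effect is not a randomised comparison.* It is one, but diluted when baseline is included.
- *That the false pattern arises in half of null trials.* The 50% counts either arm alone; the misleading direction is 25% at most.
- *That six months must be the sole deciding time.* The hypothesis names three and six months together.

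The defence does not remove what the article itself states: a hypothesis about one arm, significance tests that match that wording, and a main effect named beside the interaction with no order between them.

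**Conclusion.** The point holds in this limited form. The plan includes a valid randomised contrast, the GEE interaction, but sets it beside within-arm tests that are not randomised comparisons and a main effect that may be diluted. The hypothesis as worded points to the within-arm tests.

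The size is up to 25% for the misleading 'intervention only' pattern, given equal change in both arms and 50% power per arm. The dilution to 75% (28 to 21 points) assumes a constant effect and simple averaging on the percentage-point scale; the article states no link or coding for the GEE. The variance ratios of 0.65 to 0.85 rest on assumed correlations, continuous outcomes and no clustering. They apply to outcomes such as the knowledge and belief scores and do not transfer directly to the binary primary outcomes, so no precision gain of a stated size can be claimed there.

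**What to change.** 1. Reword the hypothesis in the Introduction so that each gain is compared with control.
2. In section 2.13, state that effectiveness is judged on the between-arm contrast at the follow-ups already named, three and six months. Take it from the GEE clustered on school, with follow-up values as outcome and the baseline value of that outcome as covariate. Constraining the arm means to be equal at baseline is an alternative.
3. Report within-arm change descriptively, without Cochran's Q or repeated-measures ANOVA as tests.
4. Do not interpret a group main effect that includes the baseline occasion.

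The cost is wording and model code. The baseline values are already collected, and no new data or participants are needed.

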### 2.14. Ethical Consideration

Ethical clearance was obtained from Jawatankuasa Etika Universiti Untuk Penyelidikan Melibatkan Manusia (JKEUPM) at Universiti Putra Malaysia [Ref No. FPSK(EXP16)P151] and the participating schools. This study will follow the ethical criteria throughout its entire procedure. Participants will be assured that their participation in the study is voluntary, and that they have the full right to withdraw from the study at any time they please. A participant consent form will be signed by each participant prior to conducting the survey. Data will be held in a confidential and anonymous manner. This study was registered at ACTRN: ACTRN12618000173291).

